### Intervention outcomes

Intervention outcomes will gauge the effects of the intervention Veteran health outcomes (e.g., reduction in 30-day readmissions and Emergency Department visits). Due to restrictions of the funding agency, we cannot use a randomized design. Therefore, we are using a rigorous non-randomized design. We will conduct a difference-in-differences analysis using similar VA facilities as a control. Facilities will be matched based on their propensity for intervention assignment. Propensity scores will take into account potential confounders including both summarized patient and facility-level factors such as percent rurality, size, readmission rates, and patient risk factors. Our primary outcome will be 30-day readmission and Emergency Department visit rate. We will compare 30-day readmission and Emergency Department visit rates during a defined pre-intervention period at both intervention and control sites, and again beginning 6 months after implementation. We will also conduct an ROI analysis of the TNP, comparing the costs of implementing the program and the costs of the TN with reductions in post-discharge utilization costs. Finally, we will measure client outcomes like Veteran satisfaction.

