## Methods

### Description of intervention

The TNP is an intervention carried out with a Transition Nurse (TN) in collaboration with a hospitalist site champion at each intervention site. The intervention is based on the Ideal Transitions of Care (ITC) framework [3] and consists of four core components. These are (1) pre-discharge assessment of patient understanding of self-care, medications, supports for post-discharge care, and obtaining a follow-up appointment; (2) structured post-discharge interactive communication between the hospital and primary care team alerting the primary care team of discharge; (3) a follow-up call to the patient within 48 to 72 h of discharge to confirm attendance to the follow-up appointment with the PCP, reinforce medication and self-care education provided at discharge, and assess symptoms and concerns; and (4) build knowledge and capacity at both the tertiary and primary care site to deliver improved care to future rural Veterans. The TNP was piloted in Denver between 2014 and 2016 with encouraging results such as reduced hospital readmissions and reduced costs relative to a control population [11]. Based on the success of the pilot, the TNP was funded by the VA Office of Rural Health with the support of the Veterans Health Administration (VHA) Office of Nursing Services for expansion to additional tertiary VA sites over the next 5 years.

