Implementation and sustainability infrastructure	▪ Existing processes and systems ▪ Current transition process ▪ Existing relationships and collaboration ▪ Plan for sustainability	▪ National level VA quantitative data ▪ Key informant interviews
Organizational characteristics	▪ Management support ▪ Shared goals and cooperation ▪ Inter-facility communication	▪ National level VA quantitative data ▪ Process mapping ▪ Brainwriting ▪ Key informant interviews
Patient characteristics	▪ Demographics ▪ Rural veteran readmission dates	▪ Key informant ▪ Brainwriting ▪ Veteran interviews ▪ Quantitative data on 30-day readmissions

We will employ process mapping to understand the current discharge process for rural Veterans and inform the implementation process [18]. We will validate process maps using adapted ethnographic observations on-site visits [19]. During adapted ethnographic observation, qualitative analysts will join medical teams on rounds and observe the patient discharge process. Team members will collect information on the process, interactions among providers and between providers and patients, and contextual information on the atmosphere. Process maps will also aid in return on the investment (ROI) analyses by identifying each role involved in the discharge process, the steps in the process, and time and resources required to complete each step in the discharge process.

Key informant interviews with providers at VA tertiary hospitals and rural PACT clinics will identify attitudes and beliefs, initial reactions to the TNP, barriers and facilitators to implementation of the TNP, and participant perspectives on the potential value of the program. Interviews will be summarized for each site and used to inform site visit data collection. In particular, interviews will determine which areas of the discharge process need clarification or confirmation and identify remaining questions.

Finally, during pre-implementation site visits, we will conduct a brainwriting activity [20, 21]. The brainwriting activity will be used to clarify the rural patient discharge process at each site, to identify perceived failure points in the implementation of TNP and to consider strategies to overcome these barriers. Site visits provide the opportunity to verify what we learn in key informant and process map interviews.

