#### Implementation

Our implementation strategy uses internal and external facilitation [25] and audit and feedback [25, 26] to encourage real-time adaptation of the intervention to each site. In our intervention, external facilitation will be conducted by a team in Denver. The primary investigator in Denver (RB) will meet with individual site leadership and leverage relationships with the Office of Rural Health and the Office of Nursing Services. Internal facilitation is conducted by the hospitalist champion, who will receive data from the team in Denver and have an on-the-ground role in establishing successful implementation of the program. Each site must complete the four core components of the intervention but will individualize the intervention by determining how the intervention best fits their needs and local context. For instance, each site will be responsible for identifying the high-risk rural patient population they will enroll, as each site has more rural Veteran hospitalizations (more than 1000 annually at each site) than the transition nurse can likely enroll (pilot data suggests enrollment of 250–350 rural Veterans annually).

In the first month of implementation, the TN at each site will participate in a regular teleconference with facilitators in Denver to identify barriers to intervention uptake and formulate solutions. The teleconference will serve to support the TNs as they begin enrolling patients in the program, to continually identify barriers to the program and to promote a community of practice. The Denver team will conduct a site visit 6 months after the initial implementation on TNP. The purpose of this site visit is to understand local context in order to better assist with remaining implementation barriers and to evaluate implementation fidelity. This is part of our audit and feedback strategy. By monitoring implementation at each site and assessing barriers as they arise, we will collect actionable data to share with the hospitalist champions that can be used to customize the TNP to each site. For example, we will share with each site the number of Veterans admitted, the number of Veterans who receive all components of the intervention, the time required to enroll Veterans in the program, and hospital readmission rates on a monthly to quarterly basis.

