### Implementation outcomes

We will assess both intervention outcomes and implementation outcomes [27, 28]. We will use the RE-AIM framework [29] to measure implementation outcomes (see Table 2).

**Table 2 Tab2:** RE-AIM measures in the rural transition nurse program

RE-AIM measures	TNP definition	Measurement
R—Reach	▪ Proportion of eligible rural Veterans enrolled at each site	▪ Number of Veterans enrolled each month ▪ Proportion of eligible Vets enrolled
E—Effectiveness	▪ Primary outcome is emergency department visits and hospitalizations in the 30 days following index discharge; Cost of utilization (ED/hospital); Satisfaction of Veterans and providers	▪ Hospital readmission rates ▪ Return on Investment ▪ Provider satisfaction surveys ▪ Qualitative semi-structured interviews ▪ Veteran satisfaction surveys
A—Adoption	▪ Proportion of inpatient providers that refer eligible Veterans to the TN for enrollment in the TNP ▪ Proportion of PACT providers that complete communication (*close communication loop through Lync, email, phone*) for care coordination with the TN as part of the TNP	▪ Number of Veterans enrolled each month ▪ Proportion of eligible Vets enrolled, 6 months after enrollment begins, and 1 year after enrollment begins
I—Implementation	▪ Evaluating what components of the manual and toolkit have been implemented and how they have been adapted (using Stirman framework)	▪ Regular phone calls with TNs will identify adaptations, barriers, and facilitators to implementation ▪ Survey to measure TN and Hospital Champion view of program ▪ Observational assessment of TN competency and adherence to TNP core components, as well and pre and post-test ▪ Semi-structured interviews with TNs, Hospital Champions, inpatient and PACT clinicians, and Veterans to identify internal and external factors that affect TNP implementation, as well as barriers and facilitators to implementation ▪ Measurement of adaptations using real-time tracking with and adapted Stirman framework
M—Maintenance	▪ Funding or expansion of TN role at expansion sites after 3 years of funding	▪ Return on investment ▪ Continued use and improvement of TNP program

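### The return-on-investment rule counts only utilization after discharge, although a mandatory part of TNP is delivered during the index stay, so any change in index-stay cost falls outside it

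*Protocol article*

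**What the plan says.** **The ROI rule.** The Intervention outcomes section describes the ROI as "comparing the costs of implementing the program and the costs of the TN with reductions in post-discharge utilization costs". The cost side is the program and the transition nurse. The benefit side is utilization after discharge.

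**When the intervention acts.** The first of the four core components (Description of intervention) is "pre-discharge assessment of patient understanding of self-care, medications, supports for post-discharge care, and obtaining a follow-up appointment". It takes place while the Veteran is still in hospital. It is not optional: under Implementation, "Each site must complete the four core components of the intervention".

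**When the outcomes start.** Table 2 (Effectiveness) states: "Primary outcome is emergency department visits and hospitalizations in the 30 days following index discharge". The Intervention outcomes section agrees: "Our primary outcome will be 30-day readmission and Emergency Department visit rate". Table 2 also lists the cost of ED and hospital utilization, without naming the index stay.

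**What the ROI is for.** Table 2 lists return on investment under Effectiveness and again under Maintenance, which is defined by continued funding or expansion of the nurse role after three years. The Abstract says the findings will go into a toolkit to guide wider scale-up.

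Length of stay, bed-days and time to discharge are not named in the article as an outcome, a cost, a feedback measure or a matching factor.

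**The concern.** The period over which the program can change hospital use is wider than the period over which the ROI counts it. A required inpatient step, delivered through a transition nurse at each site, could plausibly change when a patient leaves. Better planning might bring discharge forward, or an added step might push it back. Either would change hospital cost, and the stated comparison would register neither.

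What is at stake is the economic conclusion. If stays lengthen, the stated ROI is too favourable; if they shorten, it misses a real saving. The ROI is one of the measures attached to the funding question, so its boundary should cover the hospital costs that the program can itself move.

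**Working it through.** **No figure to reproduce.** The article gives no readmission rate, effect size, length of stay, unit cost or ROI value. Of the pilot it says only that readmissions and costs were lower than in a control population. What can be checked is whether any listed item fills the gap, and how large a change in stay would matter.

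**Step 1. Does another item cover index-stay cost?** There are three candidates.
- Process maps (Pre-implementation) support the ROI by recording "the steps in the process, and time and resources required to complete each step in the discharge process". They describe the existing process in staff time and resources, not patient bed-days compared with control sites.
- Site feedback (Implementation) includes "the time required to enroll Veterans in the program". This is nurse workload at intervention sites, with no control comparison.
- The utilization cost in Table 2 could in principle include the index stay, but it does not say so, and the ROI sentence refers to post-discharge use.

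None of them measures a change in index-stay cost against controls.

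**Step 2. What change in stay equals the readmission bed-days saved?**

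Break-even change per enrolled Veteran = absolute reduction in readmission risk × days per readmission.

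Both inputs are assumptions: a reduction of 2 to 5 points and 4 to 6 days per readmission.
- Low: 0.02 × 4 = 0.08 day (1.9 hours)
- Middle: 0.03 × 5 = 0.15 day (3.6 hours)
- High: 0.05 × 6 = 0.30 day (7.2 hours)

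Wider assumptions (baseline risk 10 to 20%, relative reduction 10 to 30%, 4 to 6 days) give 0.10 × 0.10 × 4 = 0.04 day up to 0.20 × 0.30 × 6 = 0.36 day.

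**Step 3. Per site and year.** The article expects 250 to 350 enrolled Veterans a year. At 300, in the middle case, bed-days saved are 300 × 0.03 × 5 = 45, and a mean change in stay of 0.15 day is 300 × 0.15 = 45 bed-days.

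The calculation is in bed-days. It carries over to cost only if an index day and a readmission day cost the same. It also leaves out ED savings, which would raise the break-even.

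**Step 4. How precisely could length of stay be estimated?** Wave 1 has five sites, so about 5 × 300 = 1,500 enrolled Veterans a year. Assume an SD of 4 to 5 days, 1,500 patients in each of the four site-by-period cells, and no clustering. The 95% half-width of the difference-in-differences is 1.96 × SD × √(4/1,500):
- SD 4: 1.96 × 4 × 0.0516 = 0.40 day
- SD 5: 1.96 × 5 × 0.0516 = 0.51 day

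Clustering within five sites would widen this. The estimate could rule out a large change in stay but could not separate 0.15 day from zero.

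**The case against.** The strongest reply is that this is a condensed article. Its outcome lists are open-ended, and a balancing measure is the sort of item left to the full protocol or analysis plan. That stands for the absence of length of stay from the outcome list, which alone would not be a finding. It does not dispose of the ROI sentence, which states what is compared with what and limits the benefit side to the period after discharge.

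Second, no passage makes discharge wait for the nurse or for the follow-up visit. Obtaining an appointment means booking it. Sites are to be told how many Veterans received every component, so incomplete delivery is foreseen. That stands, and the effect on stay is a possibility in either direction.

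Third, a reader might infer that a delay would cancel the whole saving and go unseen. The documents do not support this. The break-even rests on assumed inputs and omits ED savings. The facilitation calls, the six-month site visit and the clinician interviews could also bring delays to light, although they would not measure them against controls.

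Fourth, a reader might infer that a change in stay biases the primary outcome. It does not. If TNP alters the stay and thereby readmission, that is part of the program's effect. Secular trends in stay shared with the control sites are what the matched comparison is meant to remove.

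Finally, length of stay would be estimated too imprecisely to detect the break-even amount. That is correct, and it governs how the result should be reported.

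**Conclusion.** The point holds as a limited improvement to the economic evaluation. As stated, the ROI excludes any change in index-stay cost, although a required component is delivered during that stay, and no other listed item measures that cost against controls. The omission could bias the ROI in either direction.

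The size is illustrative. A mean change of about 0.08 to 0.30 day per enrolled Veteran would equal the readmission bed-days saved, given a 2 to 5 point reduction, 4 to 6 days per readmission, equal cost per day, and ED savings set aside. The article supplies none of these inputs. There is no evidence here that TNP prolongs the stay, and no defect in the primary outcome.

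**What to change.** In the Intervention outcomes section and in the Effectiveness row of Table 2:

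1. Add index length of stay as a balancing measure, analysed in the same difference-in-differences with the same sites and periods. Report it as an estimate with a 95% confidence interval. Do not present it as a test of no delay: a non-significant result at this sample size would say little about a change of a few hours.
2. Report the ROI twice: once as now stated, and once with utilization cost counted from index admission to 30 days after discharge.

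The cost is a few lines of wording and one further variable, with its cost, from the index hospitalization record. The downside is that the wider ROI will be less precise, because it includes the variation in index stays, and it may be less favourable. Showing both versions lets the funder see how far the conclusion depends on the boundary.

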## Discussion

The TNP is an innovative intervention with the dual goals of (1) improving the transition of care for rural Veterans hospitalized at tertiary VA hospitals and (2) testing a novel application of PRISM to assess contextual elements and tailor the intervention to individual sites. This study represents a robust application of the PRISM framework to a novel intervention. As a type II hybrid intervention-implementation study, we are also assessing novel implementation strategies combining internal and external facilitation and audit and feedback. Our implementation strategy is unique in its use of PRISM to integrate data from a variety of sources in a pre-implementation evaluation with the goal of providing real-time feedback to sites to enhance the impact adoption, implementation, and impact of the TNP.

The TNP builds on components of existing successful Transition Nurse Programs, such as the Department of Veterans Affairs Coordinated Transitional Care (C-Trac) program [35, 36]. C-Trac utilizes nurse case managers to work with patients on care coordination after discharge to community settings from a VA hospital. Like the TNP, C-Trac involves direct communication between the nurse case manager and patients via a post-discharge follow-up call. TNP builds on this program by promoting relationship building between the TN at VA tertiary hospitals and nursing staff at rural PACT sites. The creators of C-Trac used a modified version of the Replicating Effective Programs (REP) implementation theory model to adapt C-Trac to different contexts. REP is most commonly used at the population level rather than the hospital level and begins with the identification of a local site champion and documentation of existing process, followed by a pre-implementation phase that focuses on stakeholder engagement and coaching, identification of barriers, staff training, and also guiding stakeholders in formally adapting programs and documenting modifications [37]. We feel that PRISM is more appropriate for our intervention because it has a greater focus on understanding local contextual factors and organization, allowing for adaptations to diverse and unique environments. PRISM also includes the RE-AIM framework for evaluation. In our approach, external facilitators monitor the intervention using RE-AIM measures and feed the data to internal facilitators, allowing them to make targeted modifications to the intervention when necessary.

PRISM has proven a useful framework for several interventions. Liles et al. [13] used PRISM to explore internal and external barriers to colorectal cancer screening. They were able to identify barriers to colorectal screening at the staff, provider, and patient levels through stakeholder interviews, and were able to implement a program that addressed these specific barriers. Similarly, Beck et al. [12] used PRISM to assess barriers and facilitators in focus groups. As far as we know, our study is the first application of PRISM to assess context, barriers, and facilitators using data from such a wide variety of sources. Our use of PRISM to integrate data from multiple sources is also unique. We are unaware of another intervention using PRISM as a data reduction tool.

This study represents a robust application of the PRISM framework to a novel intervention. Results of our analysis will inform the utility of the PRISM framework for developing better implementation and evaluation strategies. Our multi-source data will allow us to assess the utility of our pre-implementation strategies and determine which are most successful, and to assess the utility of our intervention training and implementation strategies. Our use of the Stirman framework [34] for tracking modifications to the intervention as well as RE-AIM [33] for measuring program outcomes will allow us to assess the reach, effectiveness, adoption, implementation, and maintenance of the program in real time. In each subsequent wave of implementation, we will be able to use this information to enhance external facilitation and may be able to utilize novel study designs or new strategies when appropriate. Our use of standardized frameworks will make our findings applicable to the development, adaptation, and dissemination of new health interventions.

The primary focus of the TNP is to improve the transition of care for rural Veterans. Successful implementation will lead to reduced hospital readmissions through improved follow-up care and communication between hospitals and rural PACT sites. Our findings will have implications for the development of programs addressing transitions of care for vulnerable patient populations.

## Abbreviations

AAACN: American Academy of Ambulatory Care Nursing
CAPE: Center for Advancing Professional Excellence
CCTM: Care coordination and transitions management
C-Trac: Department of Veterans Affairs Coordinated Transitional Care Program
ITC: Ideal Transitions of Care
PACT: Patient Aligned Care Team
PCP: Primary care provider
PRISM: Practical Robust Implementation and Sustainability Model
RE-AIM: Reach, Effectiveness, Adoption, Implementation, and Maintenance Framework
REP: Replicating Effective Programs
TN: Transitions nurse
TNP: Transitions nurse program
VA: Veterans Health Administration
VHA: Veterans Health Administration
